### Timeline

For the Self-Management study, eligible patients and their informal caregivers will be randomized towards the Self-Management Intervention (SMI) or education intervention after baseline measurement T0. Both SMI and education intervention have a duration of 10 weeks and post-treatment measurement (T1) will take place at 3 months after T0. Two follow-up measurements (T2 and T3) will take place at 6 and 12 months after T0. For the Augmented CBT study, eligible patients will be randomized towards the Augmented CBT intervention the computerized cognitive training intervention after baseline measurement T0. Post-treatment measurements (T1) will take place 4 months from T0, and two follow-up measurements (T2 and T3) will take place 10 and 16 months from T0. Cost measurements for both studies are presented in Figure 3. At all measurement points, cost data will be asked retrospective varying from 2 to 6 months retrospective.

**Figure 3 F3:**
[figure not shown]
**Cost measurements Self-Management study (top) and Augmented CBT study (down)**.

### Interventions

The SMI is designed as an effective proactive coping group intervention for both stroke patients and their informal caregivers, with a duration of ten weeks [25]. The intervention, including seven group sessions, will be provided by two specially trained therapists experienced in group counselling and working with brain injury patients. The sessions will be organised in the participating institutions. Group sessions are aimed at setting goals and attaining them. These goals relate to different themes, i.e. social support and relations, participation in society, and negative emotions. Six group sessions (two hours each) will be held in participating hospitals during the first six weeks and one booster session (for exchanging experiences and repeating theoretical concepts) will be held at 10 weeks from baseline. The control group will receive an education intervention aimed at providing passive information. One trained health care professional will provide three group sessions (one hour each) in the first 6 weeks concerning different themes (i.e. the brain, a stroke, and prevention of a recurrent stroke) and a booster session at week nine from baseline; all are held in the participating institutions.

The Augmented CBT treatment will focus on registering, recognising and altering mood, negative thoughts, cognitions and emotional symptoms that comprise depressive problems as well as anxiety. The intervention will be provided by an experienced health care psychologist in the participating institutions (10-12 sessions), where occupational therapists and/or movement therapists will be enrolled in the intervention as co-therapists (three to four sessions). The intervention is an individual therapy, in which patients are expected to participate in a total of 13 to 16 individualised sessions, in a time-span of four months. Test assistants or assistant psychologists working in the participating institution will assist execution of the control intervention programme, the computerized cognitive training programme CogniPlus, aimed at improving general cognitive functioning. Patients will participate in a total of 13 to 16 sessions in a time-span of for months, equal to the Augmented CBT intervention. The programme is self-supporting as most tasks can be executed without assistance.

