### Sample size calculation

The sample size calculation of the Self-Management study is based on a method presented by Jones et al. [21]. Based on two earlier intervention studies with the UPCC [22,23], a standardised difference was calculated representing the difference between the means/population standard deviation. The studies resulted in two different outcomes: a difference in means of .2 and .3 respectively between the groups on the UPCC and a mean SD of .35 and 0.6 respectively. Based on these studies, a standardised difference of .6 on the UPCC was used for the power calculation (.2/.35 = .57). Based on the method of Jones et al, 45 patients per group are needed based on an alpha of .5 and a power of 80%. Assuming a drop-out rate of 15%, 106 patients (2 × 53) will be recruited for this study.

Based on previous research, it has not been possible to conduct a power calculation on the HADS as the psychological intervention studies in the Cochrane review [24] all used different outcome measures and not the HADS. Hence, the sample size calculation for the Augmented CBT study will be based on other measures and is therefore identical to the sample size calculation for the Self-Management study (2 × 53 = 106).

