### Statistical analysis

The power analyses in both trial-based economic evaluations will be based on the RCTs. The primary (base-case) analyses will be performed according to the intention-to-treat principle. This means that data from all participants will be used, regardless of whether they received the intervention or not. For the analyses we will use SPSS statistical software and Excel.

Respondents for whom at least 75% of the data per measurement instrument are available will be included in the analysis. Missing data on item level will be handled using SPSS missing value analysis. Completely missing measurements will be handled using multiple imputation (MI). A baseline analysis will be performed to examine the comparability of groups at baseline for both costs and outcomes. If necessary, methods will be applied to control for differences in baseline [33]. Despite the usual skewed distribution of costs, the arithmetic means is generally considered the most appropriate measure for describing cost data [33]. Therefore arithmetic means (and standard deviations) will be presented. In case of skewed cost data, non-parametric bootstrapping will be used to test for statistical differences in costs between the intervention and control group. Non-parametric bootstrapping is a method based on random sampling with replacement based on the participants' individual data [34]. The bootstrap replications will be used to calculate 95% confidence intervals around the costs (95% CI), based on the 2.5 and 97.5 percentiles. If cost data are distributed normally, t-tests will be used.

ICERs will be calculated for both the CEA and CUA. The ICER will be calculated as follows: ICER = (Ci - Cc)/(Ei - Ec), where Ci is the annual total cost of the new intervention, Cc is the annual total cost of the comparator, Ei is the effects at the 6 month follow-up for the new intervention and Ec is the effect at 6 month follow-up for the comparator.

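### Self-Management study: both arms are treated in groups, yet the 80% power and the patient-level bootstrap assume independent patients, which is too favourable if outcomes or costs correlate within groups

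*Protocol article*

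**What the plan says.** All references are to the Protocol article, in the part on the two trial-based economic evaluations.

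- **Interventions.** The self-management arm is a group programme: "The intervention, including seven group sessions, will be provided by two specially trained therapists experienced in group counselling". The education arm is also given in groups: "One trained health care professional will provide three group sessions (one hour each) in the first 6 weeks", followed by a booster session. Augmented CBT, by contrast, is described as individual therapy.
- **Timeline.** Allocation is by patient with caregiver, not by therapy group: "eligible patients and their informal caregivers will be randomized towards the Self-Management Intervention (SMI) or education intervention after baseline measurement T0".
- **Sample size calculation.** The effect size is given as "a standardised difference of .6 on the UPCC was used for the power calculation (.2/.35 = .57"). The resulting size is "45 patients per group are needed based on an alpha of .5 and a power of 80" per cent, and then "Assuming a drop-out rate of 15%, 106 patients (2 × 53) will be recruited for this study".
- **Statistical analysis.** The economic evaluations take their power from the trials: "The power analyses in both trial-based economic evaluations will be based on the RCTs". The bootstrap is described as "random sampling with replacement based on the participants' individual data". Its percentiles give the 95% interval for costs, with t-tests if costs are normally distributed. Bootstrap simulations also supply the uncertainty around the ICER, shown as a cost-effectiveness plane and an acceptability curve.

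The article mentions no therapy-group size, ICC, design effect or other allowance for clustering.

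**The concern.** Individual randomisation followed by group treatment produces clusters after allocation. Patients in one therapy group share therapists and fellow participants, and the sessions rely on exchange between participants. Their UPCC scores, utilities and costs may therefore be more alike than those of patients in different groups, and this can happen in both arms.

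Costs have an additional route. Under Cost analysis, intervention resources are based on the registered professional time. In a group session that time is shared by those attending, so this component is largely a group-level quantity.

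If there is positive within-group correlation, 45 patients per arm carry less information than 45 independent patients. Resampling patients one by one, or applying a t-test, then gives a variance that is too small. The trial would have less than the stated 80% power, and decision makers would see a cost interval, a cloud of points and an acceptability curve that look more certain than the data warrant.

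**Working it through.** **1. Reproduce the stated sample size under independence.**
Inputs (Sample size calculation): standardised difference d = .6, power 80%, dropout 15%, equal arms. Alpha is printed as .5. That value would give 13 per arm (two-sided) or 4 (one-sided), and one-sided .05 would give 35. Only two-sided .05 fits the stated size, so I use it.

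- Normal formula: n = 2 × ((1.960 + 0.842)/.6)² = 43.6, i.e. 44 per arm.
- t-test version: 44.6, rounded up to 45 per arm.
- Dropout: 45/.85 = 52.9, rounded up to 53; 2 × 53 = 106.

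Both stated figures are reproduced. The t-test power at 45 per arm is 80.4%, so the 45 contains no hidden allowance for clustering.

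**2. Add clustering.**
Group size m and ICC are not in the article. **Assumptions:** m = 4 to 8, ICC = .02 to .05, the same in both arms.

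- Design effect: DE = 1 + (m − 1) × ICC
- Effective size per arm: 45/DE
- Correct interval width relative to the patient-level width: √DE
- Type I error of a nominal 5% test: 2 × (1 − Φ(1.96/√DE))

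| | No clustering | m = 4, ICC .02 | m = 8, ICC .05 |
|---|---|---|---|
| DE | 1 | 1 + 3 × .02 = 1.06 | 1 + 7 × .05 = 1.35 |
| Effective n per arm | 45 | 42.5 | 33.3 |
| Power, d = .6 | 80.4% | 78.0% | 67.5% |
| Width ratio √DE | 1 | 1.03 | 1.16 |
| Coverage of a nominal 95% interval | 95% | 94.3% | 90.8% |
| Type I error | 5% | 5.7% | 9.2% |

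**3. Allow for dropout within groups.**
If 15% are lost, a group of 8 leaves 8 × .85 = 6.8 analysed. With ICC .05, DE = 1 + 5.8 × .05 = 1.29, the effective size is 34.9 and power is 69.5%. The upper end of the loss is therefore slightly smaller than in the table.

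**4. Number of groups.**
45/8 ≈ 6 and 45/4 ≈ 11, so there would be about 6 to 11 groups per arm. With so few, degrees of freedom are also lost. The design-effect powers above ignore this and are, if anything, optimistic.

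**5. Check the remedies.**
Simulated normal data with 6 groups of 8 or 11 groups of 4 per arm and ICC .02 to .05 gave:

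- patient-level percentile bootstrap: coverage of about 90% to 93%;
- plain two-stage cluster bootstrap: about 97% to 98%, with intervals 32% to 41% wider, where the design effect calls for 3% to 16%;
- resampling whole groups only: about 88% to 92%, no better than the patient-level method;
- group-level analysis: near 95%, in the setting (6 groups of 8, ICC .05) where the patient-level method gave about 91%.

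**The case against.** The strongest objections, and what stands of each:

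- **The size is all assumption.** This stands. Neither m nor ICC is in the article. At the low end the loss is about two points of power and under one point of coverage; at ICC 0 there is none. A reader might infer that the patient is the wrong resampling unit whatever the ICC. That is not supported: with zero correlation, resampling patients is correct.
- **The bootstrap sentence is a textbook definition, and details belong in an analysis plan or the separate trial publications.** This stands in part. The sentence is a general description with a citation, and the clinical analysis may handle clustering elsewhere. But it is the only resampling unit the article names, the replications it describes produce the cost intervals, and the stated alternative, a t-test, also assumes independence. The power figure is likewise stated without qualification. The point rests on what the article commits to, not on a detail it leaves out.
- **Total cost need not cluster.** This largely stands. Intervention cost is one of four categories. GP and hospital care, medication, travel, informal care and productivity losses arise patient by patient. The group-level argument applies mainly to the intervention component.
- **No interval is specified for effects or for the ICER.** This stands. A reader might infer that such intervals will be too narrow, but the article names a 95% interval for costs only. For the ICER it plans a bootstrap distribution, a plane and an acceptability curve, and the point concerns those.
- **A cluster bootstrap has its own faults with few groups.** This stands for the uncorrected forms, as the simulation shows, and it shapes the fix.

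**Conclusion.** The point holds for the Self-Management study only, and conditionally. The article describes group delivery in both arms but fixes a power figure and a patient-level analysis that assume independence. For any positive within-group correlation, the 80% is too high and the uncertainty shown for costs and cost-effectiveness is too small. Only the direction follows from the documents. The size (power of about 78% to 67% at d = .6, type I error of about 5.7% to 9.2%) rests on the assumed groups of 4 to 8 and ICC of .02 to .05, applied alike to every endpoint. It does not extend to Augmented CBT, which is individual therapy, even though that study borrows the same sample size. The article does not support a claim that the trial is certainly underpowered or its intervals certainly too narrow. It should be corrected, because the plan's own description of treatment gives reason to expect some correlation and the correction is cheap.

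**What to change.** For the Self-Management evaluation:

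1. Record a therapy-group identifier for every patient in both arms. The Current study status section says data collection for the economic study is still to start, so it can be captured prospectively; it may be hard to recover later.
2. Analyse costs, UPCC and QALYs with therapy group as a random effect and a small-sample degrees-of-freedom correction. Alternatively, use a cluster bootstrap with a shrinkage or small-cluster correction, and build the plane and acceptability curve from the same replications. A plain two-stage bootstrap is not advised: it is too wide with about 6 to 11 groups per arm.
3. State the expected group size, and replace the unqualified 80% with the power of 45 per group over a stated range of group size and ICC.

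Cost: one extra data item, revised analysis wording, somewhat wider intervals and a lower stated power. No extra patients and no change to treatment.

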### Outcome measures

In Figure 2 the outcome measures of the Restore4Stroke program in general and the four studies embedded in this program are shown. The primary outcome measure for the CEA will be the increase in health status as measured by the UPCC (Self-Management study) and the HADS (Augmented CBT study). Within the CUA, the primary outcome measures are QALYs for which an indirect preference-based technique will be used. In this technique, the patient's health status will be measured by means of the EQ-5D and weights that incorporate preferences from a general population sample will be used to calculate utilities. The EQ-5D is chosen because it is a widely used quality of life instrument (nationally and internationally). The EQ-5D contains five dimensions of health-related quality of life; namely mobility, self-care, daily activities, pain-discomfort and depression/anxiety [17]. Each dimension can be rated at three levels: no problems, some problems and major problems. The five dimensions can be summed into a health state. Utility values can be calculated for these health states, using preferences elicited from a general population, the so-called Dolan algorithm [26]. The utility values derived from the Dolan algorithm will be used to compute QALYs. The Dolan algorithm has been established using a general population from the UK. In 2006, a Dutch algorithm became available [27] using Dutch tariffs instead of UK tariffs to compute QALYs.

The utilities at the three time points will be used to compute a QALY score by means of the area under the curve method. Furthermore, the EQ-5D consists of a visual analogue scale (VAS) ranging from zero (worst imaginable health state) to 100 (best imaginable health state). The reliability and validity of the EQ-5D has been studied and established [28,29]. The base case analysis will use the individual utility score of the patient based on the EQ-5D.

To estimate the health effects on informal caregivers, the CarerQOL questionnaire has been chosen. This instrument was tested positively in terms of validity and feasibility in extensive research by Hoefman et al. [20]. The CarerQol questionnaire consists of two components, namely the CarerQol-7D and the CarerQol-VAS. The CarerQol-7D refers to seven dimensions, each represented by one question on the questionnaire. The seven dimensions are: fulfilment, relational dimension, mental health dimension, social dimension, financial dimension, perceived support and physical dimension The purpose of the CarerQol 7D is to help caregivers indicate their situation with respect to a particular dimension on one of three levels (*I have no/some/a lot of..*.). The CarerQol-VAS is a visual analogue scale, where caregivers can indicate how happy they feel, ranging from 0 (completely unhappy) to 10 (completely happy). The CarerQol questionnaire will be computed at every measurement point of the Self-Management study, T0-T3.

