***Primary outcomes Restore4Stroke***													

EQ-5D^b^	s	s	s	s	s	s	s	s		s	s	s	s

HADS^c^	s	s		s	p	p	p	p	s	s	s	s	s

USER-P^d^	s	s		s	s	s	s	s	p	p	p	p	p

SS-Qol-12^e^	s	s		s	s	s	s	s		s	s	s	s

Life satisfaction	s	s		s	s	s	s	s		s	s	s	s

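### The QALY curve is to use three unnamed EQ-5D time points although each RCT measures four, so the QALY period is undefined and not aligned with the costs

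*Protocol article*

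**What the plan says.** QALYs are the primary outcome of the cost-utility analysis in both RCTs. The Outcome measures section gives the rule: "The utilities at the three time points will be used to compute a QALY score by means of the area under the curve method". The three points are not identified.

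The EQ-5D row of Table 1 begins "EQ-5D^b^ s s s s s s s s". These eight entries are T0 to T3 in Self-Management and T0 to T3 in Augmented CBT. The Timeline dates them. For Self-Management, "post-treatment measurement (T1) will take place at 3 months after T0" and "Two follow-up measurements (T2 and T3) will take place at 6 and 12 months after T0". For Augmented CBT, "Post-treatment measurements (T1) will take place 4 months from T0, and two follow-up measurements (T2 and T3) will take place 10 and 16 months from" baseline.

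The Statistical analysis section defines the ICER for both the cost-effectiveness and the cost-utility analysis, with total costs over a year and effects at the six-month follow-up.

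On the tariff, the Outcome measures section says "The utility values derived from the Dolan algorithm will be used to compute QALYs" and discloses that "The Dolan algorithm has been established using a general population from the UK". It then adds "In 2006, a Dutch algorithm became available" and gives that algorithm no role.

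**The concern.** An area under the curve is fixed by its time points. The article states how many there are, and that number conflicts with its own measurement schedule. Followed literally, the rule discards one measured EQ-5D score per patient without saying which.

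The choice decides which period the QALY covers and how much weight each visit carries. If it is made after the data are seen, the primary cost-utility outcome could be chosen from several candidates. If the QALY period differs from the cost period, the numerator and denominator of the cost per QALY refer to different stretches of time.

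**Working it through.** **Step 1: the plan's count.** The Outcome measures section says three points. Table 1 shows four per RCT, so the figure of three is not reproduced for either trial.

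**Step 2: period covered by each choice of three** (last month minus first month, from the Timeline).

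| Points used | Self-Management | Augmented CBT |
|---|---|---|
| T0, T1, T2 | 6 − 0 = 6 months | 10 − 0 = 10 months |
| T1, T2, T3 | 12 − 3 = 9 months | 16 − 4 = 12 months |
| T0, T1, T3 | 12 months | 16 months |
| T0, T2, T3 | 12 months | 16 months |
| All four | 12 months | 16 months |

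Two of the four choices shorten the period. The other two keep it and use a coarser curve.

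**Step 3: weights with all four points.** By the trapezoidal rule, each interval of h months adds h/24 years to the weight of both its end points.

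- Self-Management (intervals 3, 3, 6): 3/24 = 0.125; (3+3)/24 = 0.250; (3+6)/24 = 0.375; 6/24 = 0.250. The sum is 1.000 year.
- Augmented CBT (intervals 4, 6, 6): 4/24 = 0.167; (4+6)/24 = 0.417; (6+6)/24 = 0.500; 6/24 = 0.250. The sum is 1.333 years.

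**Step 4: effect on the QALY difference.** The article gives no utilities, so these between-arm differences at T0, T1, T2, T3 are assumptions: sustained (0, 0.05, 0.05, 0.05), fading (0, 0.05, 0.025, 0) and late (0, 0, 0.025, 0.05). Each gain is the sum of weight × difference. For example, Self-Management, sustained, all four points: 0.05 × (0.250 + 0.375 + 0.250) = 0.04375. With T0, T1, T2 the weights are 0.125, 0.250, 0.125, which gives 0.05 × 0.375 = 0.01875.

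| QALY gain | All four | T0-T1-T2 | T1-T2-T3 | T0-T1-T3 | T0-T2-T3 |
|---|---|---|---|---|---|
| Self-Management, sustained | 0.0438 | 0.0188 | 0.0375 | 0.0438 | 0.0375 |
| Self-Management, fading | 0.0219 | 0.0156 | 0.0156 | 0.0250 | 0.0125 |
| Self-Management, late | 0.0219 | 0.0031 | 0.0219 | 0.0188 | 0.0250 |
| CBT, sustained | 0.0583 | 0.0333 | 0.0500 | 0.0583 | 0.0458 |
| CBT, fading | 0.0333 | 0.0271 | 0.0250 | 0.0333 | 0.0167 |
| CBT, late | 0.0250 | 0.0063 | 0.0250 | 0.0250 | 0.0292 |

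With a sustained difference and costs held fixed, T0-T1-T2 raises the cost per QALY by a factor of 0.04375/0.01875 = 2.33 (Self-Management) or 0.0583/0.0333 = 1.75 (CBT). Other choices change little or nothing, and some raise the gain.

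**Step 5: set against the ICER definition.** Annual costs match a 12-month QALY in Self-Management. Effects at six months would instead point to T0-T1-T2. In CBT no measurement falls six months after T0 (T2 is six months after T1), and a full 16-month QALY would exceed annual costs by four months. The Valuation section gives a further account: it treats follow-up as shorter than a year, whereas the Timeline runs to 12 and 16 months.

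**The case against.** The phrase may loosely mean the three post-baseline visits, with baseline taken as the starting value. Table 1 leans that way: in Self-Management the HADS, USER-P, SS-QoL-12 and life satisfaction skip T2, while the EQ-5D and the cost questionnaire are kept there. The intention may well be to use everything. That is plausible, but the text does not say it, and the number given still conflicts with the schedule.

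A reader might infer that the QALY covers the wrong period. The document does not support this, because the points are unnamed and T0-T1-T3 and T0-T2-T3 span the whole follow-up. A reader might also take the share of months lost (25% for T1-T2-T3 in both trials; 50% or 37.5% for T0-T1-T2) as the loss of QALY gain. It is not. With a sustained difference, T1-T2-T3 lowers the gain by about 14% in both trials, and T0-T1-T2 lowers it by about 57% and 43%.

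For CBT, using all four points does not by itself repair the plan, because it puts 16 months of QALYs against annual costs. This objection stands, and the ICER definition has to change as well.

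Finally, a reader might infer that the UK tariff gives wrong values. It is an explicit, disclosed choice that nothing else in the article contradicts. The societal perspective is defined there by which costs and outcomes are included, not by whose preferences weight the health states, and the stated requirement of general-population weights is met. The tariff is therefore only a secondary point.

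**Conclusion.** The conflict between three and four time points is real in both RCTs and affects the primary cost-utility outcome. The result is an undefined QALY period (6, 9 or 12 months in Self-Management; 10, 12 or 16 months in CBT) that is not aligned with annual costs and six-month effects. It has not been shown that the period is wrong.

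The effect on the QALY gain depends on the choice of points and on the course of the utility difference. In the assumed courses it runs from none to a fall of 86% (Self-Management, late difference, T0-T1-T2: 0.0031 against 0.0219), with increases of up to 17% (CBT, late, T0-T2-T3: 0.0292 against 0.0250). These figures illustrate sensitivity and do not predict the result.

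The tariff is a cheap improvement and not an error. The article gives no tariff values, so neither the size nor the direction of its effect can be established.

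**What to change.** 1. In Outcome measures, replace the reference to three time points with a trapezoidal area under the curve over T0, T1, T2 and T3 in both RCTs, giving the months.
2. In Statistical analysis, amend the ICER definition so that costs and QALYs cover the same period in each trial: 12 months for Self-Management; for CBT, either 16 months for both or 12 months for both. For the 12-month option, interpolate the utility at month 12 as 2/3 × T2 + 1/3 × T3, since month 12 lies 2 of the 6 months from T2 to T3, and cut the costs at month 12 by a stated rule. Make the follow-up length given in Valuation agree.
3. As an improvement, score the same EQ-5D data with both tariffs and state which is base case. The Dutch tariff is preferable there, given Dutch patients and Dutch unit costs, with the UK tariff as a sensitivity analysis.

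Items 1 and 2 are short text changes and need no new EQ-5D data. Item 3 costs one extra scoring run.
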